## 5.2 Secondary analyses

### 5.2.1 Subgroup analyses for the primary outcome

The following subgroups will be examined:

- Center (one level for each center, or at least for those recruiting  $\geq 10$  children)
- Hydrocephalus at cUS before 8 DOL (Grade  $\leq 1$  vs.  $> 1$ )
- Severity of intraventricular haemorrhage, IVH, at cUS before 8 DOL (with infarction vs. without infarction)

We will assess whether the treatment effect of EPO differs among subgroups of patients by adding the subgroup factor and the subgroup  $\times$  treatment interaction to the statistical model described for the main primary analysis above (Section 5.1), except that for the subgroup "center" we will drop the random intercept per center. A significant subgroup  $\times$  treatment interaction will indicate that the treatment effect differs between subgroups (or in at least one level of the subgroup factor in case of  $> 2$  levels).

We will use the FAS with multiply imputed missing values for these subgroup analyses.

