| Coordinating Principal Investigator:     | [name]. med. [name]
Universitäts- Kinderspital beider Basel (UKBB), 4056 Basel
[contact], [contact],
Email [contact]                                                                                                                                                                                                                       |
| Objective(s)/ Outcome(s):                | Primary objective: At 5 years of age: Intelligence quotient (Kaufman Assessment Battery for Children, German version (K-ABC))
Secondary objectives:
1) cerebral ultrasound (cUS) findings until discharge
2) At term equivalent age: Brain injury score assessed on brain MRI
3) At 24 months: Mental development (Bayley III), incidence of visual, hearing and motor impairment |
| Number of Subjects:                      | In total, 120 very preterm infants have to be enrolled (n=60 verum, n=60 placebo), to achieve a target sample size of n=100 for secondary outcome MRI at term equivalent age and to achieve a target sample size of n=80 for primary outcome at 5 years of age.                                                                                                                               |
| Diagnosis and Main Inclusion Criteria:   | 1. Infants at birth < 32 weeks gestational age and/or < 1'500 g
2. IVH grade II-IV (grade IV= haemorrhagic parenchymal infarction)
3. Chronological age < 9 days of life (DOL)
4. Informed written parental consent                                                                                                                                                                  |
| Main Exclusion Criteria:                 | 1. Genetically defined syndrome
2. Severe congenital malformation adversely affecting life expectancy and/or neurodevelopment
3. A priori palliative care
4. Unlikely to participate at 5-year follow-up examination                                                                                                                                                                 |

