#### **Hypotheses:**

The alternative hypothesis for all endpoints is improvement with regard to the endpoint in the group of EPO-treatment. The null hypothesis for all endpoints is no improvement with regard to the endpoint in the group of EPO-treatment compared to the control group.

The study hypotheses are one-sided – however, the tests will be performed 2-sided yielding corresponding confidence intervals and accordingly information about the direction of a potential difference between control and treatment group.

The significance level alpha is 0.05.

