## 12.5 Determination of Sample Size

Information about effect size and standard deviation of the primary endpoint (IQ outcome at age of 5 years) can only be derived from one observational study presented by Neubauer AP et al. who investigated the effect of EPO-treatment of VLBW infants on composite IQ at 10 years.

Neubauer AP et al. included in their study all grades of IVH, also the lowest, IVH I°. However, diagnosis of IVH I° may be missed or even overestimated in very preterm infants. Neubauer AP et al. reported on no difference in infants without IVH regarding composite IQ at 10 years between EPO-treated and untreated, hence we decided to exclude infants with borderline diagnosis of IVH I° to avoid bias from misdiagnosis.

Neubauer et al. reported for the relevant group of children who suffered IVH an effect size between EPO-treated (IQ=90.3) vs. untreated (IQ=67.0) of 23, standard deviation (SD) 21,  $p < 0.01$ . Given that the vast majority of children will remain on their 5-year IQ trajectory, and there is good agreement between classification of cognitive abilities at 5 and 11 years of age, we used this continuous outcome parameter (effect size 23) for power analysis.

To determine the required sample size for the primary outcome we performed a power calculation for a 2-sample t-test assuming a significance level of  $\alpha=0.05$ ,  $SD=21$  of the outcome, and a 1:1 randomization. As result we get as required total sample size  $n=28$  (for both groups together), and  $n=38$  for a power ( $1-\beta$ ) of 0.8 and 0.9, respectively.

When assuming a smaller effect size of 10 (instead of 23), a SD of 15 (instead of 21 because IVH I° will be excluded in our study group to avoid misdiagnosis leading to a sample which is less heterogeneous with regard to the primary outcome) and a power of 0.8, the required total sample size is  $n=72$ .

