Based on the only available data of Neubauer et al. and the just mentioned reduction of the assumed effect size to 10 (instead of 23) and SD to 15 (instead of 21) we set the target sample size for visit 4, the secondary endpoint 'MRI at term equivalent age', at  $n=50$  for EPO and  $n=50$  for placebo. Given a 20% loss to follow up until 5-year,  $n=80$  will meet the primary endpoint, visit 6. This number is in line with the result of the power analysis presented above. Hence, to achieve the target sample size for visit 4 of  $n=100$  and an assumed early loss by about 15% due to e.g. death in this high-risk VLBW infant population,  $n=120$  VLBW infants with IVH II-IV have to be enrolled in this trial.

According to data of the Bundesamt für Statistik ([www.bfs.admin.ch](http://www.bfs.admin.ch)) and the Swiss neonatology register (Minimal Neonatal Dataset, MNDS, [www.neonet.ch](http://www.neonet.ch)) more than 800 very low birth weight (VLBW) infants were born each year since 2007 in Switzerland. The participating 8 Swiss neonatology level III units treat more than 80% of all VLBW infants in Switzerland ( $n>700$  per year). To increase the number of eligible VLBW infants per year, the neonatology units of the University hospitals in Berlin (Charité) and Wien will contribute, treating together about 400 VLBW infants per year. Together, at all 9 study sites, more than 1000 VLBW infants will be assessed for eligibility each year.

As this trial offers a unique chance to receive a potentially beneficial treatment for IVH, the majority of parents are expected to be sympathetic to the trial (70%). Together, to achieve a target sample size of n=80 for the primary endpoint (visit 6) a total number of 1670 VLBW infants have to be assessed for eligibility:

- assessed for eligibility n=1'6700 VLBW infants → 12% have IVH grade 2-4
- presence of IVH II-IV n=200 VLBW infants (IVH II-IV) → 15% loss due to exclusion criteria
- asked for participation n=170 VLBW infants (IVH II-IV) → 30% no parental consent
- to be enrolled in trial n=120 VLBW infants (IVH II-IV) → 15% early loss (death)
- to be analyzed at visit 4 n=100 VLBW infants (IVH II-IV) → 20% loss at 5-year follow-up
- to be analyzed at primary endpoint (visit 6) n=80 VLBW infants (IVH II-IV)

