### 3 Hypothesis

The alternative hypothesis for the primary endpoint is that EPO improves the intelligence quotient at 5 years of age compared to Placebo. The null hypothesis is no improvement with regard to the primary endpoint by EPO compared to Placebo.

Although the main study hypothesis is one-sided, we will apply two-sided tests. Estimates and confidence intervals will provide information about the direction of potential differences between the EPO and the Placebo arm.

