## 8 Handling of missing data and drop-outs

We will multiply impute missing outcome and covariate data due to death or loss to follow-up in the FAS. Multiple imputation will be performed by the R package mice ([van Buuren and Groothuis-Oudshoorn, 2011](#)), and will be applied separately at each stage of analysis (see Section 5). The imputation model will use all relevant baseline variables, the randomized treatment and outcome variables collected up to the time of analysis, potentially using correlations among outcomes for imputation in case the amount of missing data differs among outcomes. We will produce  $m=20$  imputations per missing value and analyze the 20 resulting complete data sets using Rubin's rules to pool the results.

While multiple imputation assumes missingness at random (MAR), missingness not at random can be investigated using the random indicator method proposed by [Jolani \(2012\)](#), mentioned also in [van Buuren \(2018\)](#). The latter will be used for sensitivity analysis S3.

In addition, a principal stratification approach suggested by [Hayden et al. \(2005\)](#) may be applied in order to estimate the "survivor average causal effect" (SACE), as proposed for sensitivity analysis S4.

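### SAP 5.2.1 tests subgroup-by-treatment interactions on imputed IQs, but the imputation inputs in SAP 8 do not provide for those interactions, so the estimates may be biased towards zero

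*Combined protocol and SAP*

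**What the plan says.** SAP 5.2.1 names three subgroup factors for the primary outcome: centre, hydrocephalus on early ultrasound (grade above 1 or not) and haemorrhage severity (with or without infarction). Each factor and its interaction with treatment are added to the primary model, and a significant interaction is to be read as a difference in treatment effect. One data set is named: "We will use the FAS with multiply imputed missing values for these subgroup analyses".

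SAP 8 describes how those values are produced: "The imputation model will use all relevant baseline variables, the randomized treatment and outcome variables collected up to the time of analysis". It names the R package mice, 20 imputations and Rubin's rules, and applies imputation separately at each analysis stage. It does not name the imputation method or mention interactions.

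Two other places matter. The last sentence of SAP 5.2.2 plans every secondary analysis twice, on the imputed set and on complete cases. On missing data, protocol 12.5 ends its recruitment funnel with "to be analyzed at primary endpoint (visit 6) n=80 VLBW infants" out of 120 enrolled, whereas SAP 5.1 speaks of 20% loss in total.

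**The concern.** An imputation model should contain every term that the analysis model tests. If IQ is imputed from treatment and subgroup without their product, the imputed IQs are drawn as though treatment worked equally in both subgroups. The interaction is then estimated from a mixture of observed children, who carry the true difference, and imputed children, who carry almost none.

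Two separate faults follow. The estimate is biased towards zero, and the SE from Rubin's rules no longer matches the real sampling spread, so the test is miscalibrated. A real difference in effect by infarction would be under-reported, and a null interaction could be misread as evidence of a uniform effect. Protocol 4.1 describes infants with grade III-IV haemorrhage as among the most severely affected, so the question is of clinical interest.

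**Working it through.** **Inputs from the documents.** "The significance level alpha is 0.05"; "Although the main study hypothesis is one-sided, we will apply two-sided tests"; "In total, 120 very preterm infants have to be enrolled (n=60 verum, n=60 placebo"; planning difference 10 IQ points and SD 15 (protocol 12.5); 20 imputations (SAP 8).

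**The plan's own figure.** Protocol 12.5: "When assuming a smaller effect size of 10 (instead of 23), a SD of 15" "and a power of 0.8, the required total sample size is" 72. Per arm, 2 × (1.96 + 0.842)² × 15²/10² = 35.3, rounded up to 36, so 72 in total. This reproduces (a t-based calculation gives 74; one-sided testing would give 56). It concerns the main effect only; no power is claimed for an interaction.

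**Missing fraction.** 1 − 80/120 = 33.3% on the protocol funnel; 20% on SAP 5.1.

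**Rough size of the bias.** If imputed values carry no interaction, the expected estimate is about the observed fraction times the truth: 2/3 × 10 = 6.7 points for a true 10 points.

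**Power before any imputation problem.** With N observed IQs and share p in one subgroup, SE = 15 × √(4/(Np) + 4/(N(1−p))). For N = 80:
- p = 0.5: SE 6.71; power for 10 points 32%; 80% power needs 18.8 points
- p = 0.3: SE 7.32; 28%; 20.5 points
- p = 0.2: SE 8.39; 22%; 23.5 points

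**Simulation.** 120 children, SD 15, 20 imputations, Rubin's rules with small-sample degrees of freedom, 1,200 trials per scenario. Assumptions not in the documents: subgroup share 30% or 50%, true interaction 0, 10 or 20 points, IQ missing completely at random, a 2-year score correlated 0.6 with IQ (0.8 in one scenario) and absent for children who died, and no centre effect. Monte Carlo error on power is about 1-1.5 percentage points.

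One third missing, 50% subgroup, correlation 0.6. The mean, SD and SE columns are for a true interaction of 10 points:

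| Method | Mean estimate | Empirical SD | Mean SE | Power, 10 points | Power, 20 points | Rejection, no interaction |
|---|---|---|---|---|---|---|
| Complete cases | 9.87 | 6.79 | 6.80 | 28.7% | 82.1% | 5.0% |
| Main effects, normal model | 6.45 | 4.55 | 6.50 | 7.3% | 45.9% | 0.3% |
| Main effects, predictive mean matching | 8.17 | 6.25 | 7.03 | 15.3% | 47.8% | 2.7% |
| Main effects, normal model plus 2-year score | 7.06 | 4.69 | 6.37 | 11.8% | 60.6% | 0.6% |
| Normal model with product term | 9.87 | 6.88 | 6.89 | 28.6% | 79.7% | 4.4% |

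With a 30% subgroup and 10 points, power is 25.6% in complete cases, 5.9-10.8% with main-effects imputation and 25.1% with the product term. With correlation 0.8, the 2-year score raises the 20-point power to 71%, still below the 82% of complete cases.

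**Shrinkage by method.** At one third missing: about 35% (normal model), 18-25% (matching), 23-29% (with the 2-year score). At 20% missing: 20-21%, 9-15% and 18-19%. At 20% missing, power for 10 points in a 50% subgroup is 36% in complete cases and 21-29% with main-effects imputation.

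**Price of the product term.** In a further simulation (35% subgroup, 10 points, one third missing, 1,500 trials), the normal model without the term gave mean 6.65, empirical SD 4.9 and pooled SE 6.8. With the term it gave 9.91, 7.1 and 7.2.

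**The case against.** The strongest reply is that SAP 8 is silent. It lists variables and fixes no functional form, so a careful analyst could add the product term within it. That stands: a reader might infer that the SAP prescribes a model without interactions, and it does not say so. But the listed inputs, used as written, produce the problem, and no subgroup-specific imputation run is foreseen.

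Second, the complete-case sentence closing SAP 5.2.2 covers all secondary analyses, and 5.2.1 sits under the heading 5.2 Secondary analyses. On that reading an interaction test without this shrinkage is already planned, including for centre. This is a fair reading but not a secure one, because 5.2.1 names only imputed data. Even if it holds, two interaction results would be reported with no rule for which governs.

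Third, the biased estimator is less variable. In the 35% case its root mean squared error is √(3.35² + 4.9²) = 5.9 points, against 7.1 with the term. That is true, but the reported SE does not reflect the smaller spread (6.8 against 4.9), so the reader gains no precision from it and the interval is centred in the wrong place.

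Fourth, the error is conservative and leaves the primary analysis untouched. Both are correct, and they limit how serious the point is.

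**Conclusion.** The point holds as a gap in specification with a predictable consequence. If imputation follows the listed inputs as main effects, interaction estimates shrink by about 18-35% at one third missing and about 9-21% at 20% missing. The test then runs well below its nominal level (about 0.3-2.7%). At one third missing, power for 10 points falls from about 25-30% to 6-15%; for 20 points in a 50% subgroup it falls from about 82% to 46-61% (71% if the 2-year score correlates 0.8 with IQ). These sizes rest on the simulation assumptions listed above.

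Three stronger readings are not supported. One third is not the general size of the shrinkage: it applies to normal-model imputation at the protocol's loss, and is smaller with matching, with 2-year scores or at 20% loss. Imputation does not create the low power: complete cases give only 22-32% for 10 points by formula, and the omission makes that worse. Nor does it threaten false subgroup claims, since the error runs towards no difference.

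**What to change.** Before the 5-year analysis, amend the SAP as follows.

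- In Section 8, state that for each binary subgroup analysis IQ is imputed in mice with that subgroup's treatment-by-subgroup product term in the model.
- For centre, and for any subgroup too small for a stable product term, base the interaction test on observed IQs. The frequency of early hydrocephalus above grade 1 is not given, so this may apply there.
- State in 5.2.1 whether the complete-case run in 5.2.2 covers the subgroup analyses, and which result governs, so that the two sections agree.
- Label the subgroup tests exploratory. Leave the main primary analysis unchanged.

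The cost is one extra imputation run per binary subgroup and a larger sampling SD of the interaction estimate (about 4.9 to 7.1 points in the 35% case), with little change in the reported SE (6.8 to 7.2). The fix removes the bias and restores calibration. It does not make the tests well powered: about 25-29% for a 10-point interaction at one third missing.

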### 5.2.2 Analysis of secondary outcomes

Continuous secondary outcomes will be compared between treatment arms (EPO vs. Placebo) using a linear mixed-effects model with "treatment" as fixed explanatory factor and a random intercept per "center", like the primary outcome. We will report the resulting estimates of the EPO treatment effects together with 95 % confidence intervals and p-values (unadjusted and adjusted for multiple testing). The model assumptions will be checked by visual assessment of the residuals and either log-transformation of the outcome or the use of a generalized linear mixed-effects model (e.g. with Poisson error) may be considered in case of violations. For the outcome BSID-III at two years (combined score and subscores) we will add a sensitivity analysis to adjust for additional covariates, as specified as sensitivity analysis S1 for the primary outcome (Section 5.1). Moreover, the methods described for sensitivity analyses S3 and S4 may also be applied to continuous secondary outcomes.

Binary secondary outcomes will be compared between treatment arms (EPO vs. Placebo) using a generalized linear mixed-effects model with binomial error (referred to as logistic regression in the study protocol), again with "treatment" as fixed explanatory factor and a random intercept per "center". The resulting odds ratio (OR) estimates of the EPO treatment effect will be reported together with 95 % confidence intervals and p-values. Binary secondary outcomes from cUS (severe brain injury, posthaemorrhagic hydrocephalus grade  $> 1$ ) were measured three times: at baseline, 28 DOL and 36 weeks PMA. The measurement taken at baseline and the time of outcome measurement (28 DOL vs. 36 weeks PMA) will be used as additional fixed explanatory variables in the model. A random intercept per patient (nested in center) will be added to the model, to account for the non-independence of the repeated outcome measurements. In addition, we will assess the treatment  $\times$  time interaction. We will use the R package lme4 (Bates et al., 2015) to fit the models for binary outcomes and derive p-values using likelihood ratio tests.

Developmental outcome (normal, non-normal or dead) will be compared between treatment arms by a chi-squared test and will also be analyzed as binary outcome (normal vs. non-normal or dead) as described above.

The length of stay (LOS) in hospital will be analyzed as time to hospital discharge, using a competing risks model to account for the competing risk of in-hospital death (as recommended in [Brock et al., 2011](#)). We will use the R package survival ([Terry M. Therneau and Patricia M. Grambsch, 2000](#)) to fit a cause-specific proportional hazards model. For the sake of simplicity, we will include treatment and center as fixed effects (no random center effect).

We will once use the multiply imputed FAS and once the complete cases of the FAS for all secondary analyses.

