  2. Any IVH, including GMH and PHI
  3. Ventricle dilatation < 97 centile according to Levene
- Severe brain injury will be defined as:
  1. IVH with ventricular dilatation
  2. Posthaemorrhagic ventricular dilatation > 97 centile
  3. Parenchymal haemorrhagic infarction (PHI)
  4. Cystic PVL
  5. Cerebral atrophy
  6. Cerebellar haemorrhage

Definition of ventricular dilatation, including a normogram for the 97th centile and 4 mm above 97th centile: The ventricular index is the distance between the lateral wall of the body of the lateral ventricle to the falx in the coronal plane just posterior to the foramen of Monro.

(Levene, Arch Dis Childh 1981;56:900-904)

[figure not shown]

Course of haemorrhage until DOL 28:

Posthaemorrhagic hydrocephalus, graded 0-3:

- 0) Restitution ad integrum – no remaining lesions, date of last follow up
- 1) Persisting posthaemorrhagic hydrocephalus without any drainage
- 2) Persisting posthaemorrhagic hydrocephalus with repetitive but transient csf-drainage, indicate if LP, or Rickham, or both and indicate for how long
- 3) Posthaemorrhagic hydrocephalus with permanent csf-drainage, e.g. VP-Shunt

Convulsions:

- If present and/or any antiepileptic therapy, if yes specify treatment including duration
- Other abnormalities or medications related to haemorrhage
- if yes specify

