## **6.6 Visit 3, postmenstrual age of 36 completed weeks gestation, 36 0/7**

At this time point the following items will be recorded, also given on SecuTrial form Visit 3. This includes items first recorded at GA 36 0/7 and a summary of treatments and complications of whole hospitalisation. If discharge home is later, some items have to be completed immediately after discharge:

- Date of visit
- Weight (g) and SD from mean weight at GA 36 0/7
- Head circumference (cm) and SD from mean length at GA 36 0/7
- Length (cm), SD from mean length at GA 36 0/7
- Hct in % and first Hb in g/dl at GA 36 0/7

cUS at GA 36 0/7, graded in normal, moderately abnormal and severely abnormal brain injury according to definitions given in visit 2

Course of haemorrhage until visit 3:

Posthaemorrhagic hydrocephalus, graded 0-3:

- 0) Restitutio ad integrum – no remaining lesions, date of last follow up
- 1) Persisting posthaemorrhagic hydrocephalus without any drainage
- 2) Persisting posthaemorrhagic hydrocephalus with repetitive but transient csf-drainage, indicate if LP, or Rickham, or both and indicate for how long
- 3) Posthaemorrhagic hydrocephalus with permanent csf-drainage, e.g. VP-Shunt

Convulsions:

- If present and/or any antiepileptic therapy, if yes specify treatment including duration
- Other abnormalities or medications related to haemorrhage
- if yes specify

Other clinical parameters until visit 3:

- Respiratory support at DOL 28 to define if mild BPD is present; indicate if FiO2 > 0.21 and/or any form of positive pressure support, CPAP or mechanical ventilation
- Respiratory support at 36 0/7 to define if moderate or severe BPD is present. BPD moderate if FiO2 > 0.21 but <0.3; BPD severe if CPAP or mechanical ventilation and/or FiO2 ≥ 0.3. These definitions are in accordance with those of the NIH adapted by the Swiss society of neonatology.
- Supplemental O2
  - Last day of supplemental O2, give date
  - Total days of supplemental O2
  - Total days of mechanical ventilation
  - Total days of CPAP
- Surfactant treatment
- Treatment with postnatal steroids, given or not given
- PDA prophylaxis, if yes indicate if indomethacin or ibuprofen
- PDA treatment, if yes indicate if indomethacin, ibuprofen, or surgical ligation
- Pneumothorax, if yes, localization
- NEC, date of onset
- FIP, date of onset
- Sepsis, date of onset, indicate if blood culture positive

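### For hydrocephalus grade >1 the planned mixed model reads one largely cumulative outcome twice, so its default lme4 fit leaves the treatment test with little power and an odds ratio that cannot be interpreted

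*Combined protocol and SAP*

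**What the plan says.** SAP 5.2.2 takes two binary ultrasound outcomes, severe brain injury and posthaemorrhagic hydrocephalus grade >1, and enters the DOL 28 and 36-week readings of each infant in one binomial mixed model. Treatment, the baseline reading and time are fixed effects, and centre is a random intercept. In addition: "A random intercept per patient (nested in center) will be added to the model, to account for the non-independence of the repeated outcome measurements". The treatment × time interaction is also assessed. The fit is by lme4 with likelihood ratio tests, and "The resulting odds ratio (OR) estimates of the EPO treatment effect will be reported together with 95 % confidence intervals and p-values".

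The two outcomes are recorded differently in the protocol:

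- **Hydrocephalus.** At visit 2 (protocol 6.5) the grade stands under "Course of haemorrhage until DOL 28". At visit 3 (protocol 6.6) it stands under "Course of haemorrhage until visit 3". Grades 2 and 3 mean that CSF was drained, transiently or permanently, so the analysed cut is drainage against no drainage.
- **Severe brain injury.** The scan is graded at DOL 28 and again at 36 0/7 weeks. These are two point-in-time readings.

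For continuous outcomes SAP 5.2.2 names remedies if the model fits badly. It names none for the binary mixed models.

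**The concern.** A patient random intercept in a logistic model is estimated from how often an infant's two readings differ, and in which direction. A drainage before DOL 28 also lies within the period up to visit 3. By the form headings, an infant above grade 1 at the first reading should therefore rarely be at or below it at the second. The data then hold few discordant pairs, nearly all in one direction, and the patient variance has almost nothing to hold it down.

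Cerebral ultrasound is the first secondary objective in the synopsis, and the publication policy foresees reporting it separately and before the primary outcome. A real difference in drainage could then appear in print as a clearly non-significant result, with an enormous confidence interval and an odds ratio that no reader can use.

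**Working it through.** **Inputs from the documents.** "The significance level alpha is 0.05" (protocol 12.2); tests are two-sided (SAP 3); 1:1 allocation and nine centres (SAP 1); 100 infants, 50 per arm, with data near term (protocol 12.5). **Assumed, because the documents give no values:** event rates and the share of infants whose two readings differ.

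**1. The plan's own figure.** Protocol 12.5 gives a total of 72 for a 10-point IQ difference, SD 15 and power 0.8. Per arm, 2 × (1.960 + 0.842)² × 15²/10² = 35.3, rounded up to 36, so 72 in total. It reproduces, but concerns IQ only. No power or event rate is stated for the ultrasound outcomes.

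**2. One reading per infant, assumed example.** Placebo 10/50 then 15/50, EPO 6/50 then 9/50, with nobody reverting. At 36 weeks:

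- OR = (9/41)/(15/35) = 0.51.
- SE of log OR = √(1/9 + 1/41 + 1/15 + 1/35) = 0.48; 95% CI 0.20 to 1.31.
- Likelihood ratio statistic 1.99, p=0.16.

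**3. Same data, Laplace fit** (treatment, time and patient intercept; no centre or baseline term).

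| Infants who revert | Patient SD | LRT p for treatment |
|---|---|---|
| 0 | 81 | 0.81 |
| 1 | 35 | 0.75 |
| 2 | 20 | 0.67 |

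With none reverting, the statistic is 0.056. The OR is 0.49 with SE 3.0 on the log scale: exp(−0.71 ± 1.96 × 3.0) runs from about 0.001 to about 175.

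**4. Same data, exact likelihood by numerical integration.**

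| Patient SD held at | 2 | 5 | 10 | 20 | 40 |
|---|---|---|---|---|---|
| −log L | 80.4 | 72.0 | 69.9 | 69.45 | 69.43 |
| Conditional OR | 0.36 | 0.13 | 0.02 | 0.0005 | about 0 |

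The likelihood keeps improving as the SD grows and the conditional OR slides to zero. The treatment statistic nevertheless stays at 1.91, p=0.167, close to step 2. With 12 then 18 of 50 against 3 then 5 of 50, the exact test gives p=0.0016. The power is therefore lost through the Laplace approximation under a diverging variance, not through reading the outcome twice.

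**5. Simulation of the fuller model.** lme4 default fit, patient nested in nine centres, 50 per arm, with a baseline term for severe injury only. Grade >1 before DOL 8 was assumed almost absent, so hydrocephalus had no baseline term. The comparator is a logistic LRT on the 36-week reading of the same data.

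| Scenario (assumed) | Discordant | Median patient SD | Planned model rejects | One reading rejects |
|---|---|---|---|---|
| Hydrocephalus, 25% vs 10% | 4% | 80 | 0/8 | 5/8 |
| Hydrocephalus, 40% vs 15% | 3% | 40 | 0/11 | 10/11 |
| Hydrocephalus, 40% vs 10% | 8% | 77 | 1/8 | 8/8 |
| Severe injury | 7% | 21 | 0/13 | 7/13 |
| Severe injury | 17% | 5.5 | 39% of 18 | 56% of 18 |
| Severe injury | 28% | 1.4 | 92% of 49 | 35% of 49 |
| Hydrocephalus null, 25% both arms | 4% | 78 | 0% of 120 | 4.2% of 120 |

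The three hydrocephalus scenarios with an effect give 1/27 against 5 + 10 + 8 = 23/27. Adding the 7% severe-injury scenario gives 1/40 (exact 95% CI about 0.1% to 13%) against 30/40.

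**6. Finer quadrature.** With 25 points and a patient intercept only, the null scenario rejected in 23% of runs. This was not a reliable repair.

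**The case against.** Four points on the other side carry weight.

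- **The hydrocephalus grades are partly worded as current status.** Grade 0 means nothing remains, and grades 1 and 2 speak of persistence. An infant drained early and recovered by 36 weeks could be graded 0 at visit 3, and SAP 5.2.2 itself speaks of outcomes measured three times. This stands: strict nesting is an inference from the headings. One or two reversals do not rescue the fit in step 3, however, and the ambiguity itself needs settling.
- **A reader might infer that both outcomes are overlapping windows.** The documents do not support that. Severe injury is graded at each visit. Some of its defining lesions, such as infarction and cystic PVL, may well persist, but ventricular dilatation can appear or resolve. At 28% discordance the planned model was the better test.
- **A reader might infer that nested repeated readings destroy power in themselves.** Step 4 shows that they do not. The uninterpretable conditional OR is a separate defect and remains.
- **The checks are limited.** Event rates are assumed, the scenarios with a true effect have 8 to 49 runs each, and multiple imputation and the Holm adjustment were left out. Neither of those two procedures is designed to stabilise a runaway variance.

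SAP 5.3 also requires frequencies by arm, so the raw contrast would be visible beside the failed test. That limits the harm but does not supply a valid test.

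**Conclusion.** The concern holds for hydrocephalus grade >1. As the forms are headed, the two readings are largely one cumulative outcome. With the few discordant pairs this implies, the planned lme4 fit gives a patient SD of about 20 to 80, a treatment test that almost never rejects (1/27 against 23/27 with one reading) and an OR without meaning. This rests on assumed event rates, on sites following the cumulative headings, and on the default Laplace fit.

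For severe brain injury the concern is conditional. Failure was clear at about 7% discordance, partial at 17% and absent at 28%, and the documents give no agreement rate. Near-zero power is therefore not established for that outcome.

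It would be too strong to read this as a threat to the trial's main result: both outcomes are secondary and the IQ analysis is untouched. The analysis is wrong as written for hydrocephalus and should be changed.

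**What to change.** In SAP 5.2.2:

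- **State what the hydrocephalus grade means** at each visit: cumulative to date, or current status.
- **Hydrocephalus grade >1.** Test one outcome per infant, status by visit 3, in a logistic model with treatment, a baseline severity term (for example IVH grade) and a random centre intercept. Report DOL 28 descriptively and drop treatment × time. Alternatively, fit a marginal GEE model with robust standard errors to both times, clustered on infant, and report the marginal OR.
- **Severe brain injury.** Use the marginal GEE model on both readings, or keep the mixed model with a prespecified switch to GEE if the patient variance diverges. The trigger should be written down in advance, for example a patient SD above 10 on the logit scale.
- **Wherever GEE is used,** say how centre enters, since it has no random intercept.

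The cost is SAP wording only. Under the one-reading option, the formal DOL 28 hydrocephalus test and its interaction are lost. For severe injury, moving to a single reading could cost power if many infants change category, which is why both readings are kept there.
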